## Materials and Methods

### Context (FRAnconian Longitudinal Study of Anorexia Nervosa in Adolescents)

The body exposure intervention described in this study protocol is part of the bigger FRALANA study (FRAnconian Longitudinal study of Anorexia Nervosa in Adolescents), which is being carried out at the Division of Child and Adolescent Mental Health, University Hospital Erlangen. The FRALANA study aims to broaden the knowledge of AN pathogenesis and the understanding of underlying mechanisms of AN treatment in children and adolescents, using a multi-level approach. The FRALANA study consists of a basic and an intervention module. For the basic module, data is collected from three groups of participants (AN group, depressive control group, healthy control group), across three different points in time during and after inpatient treatment. The intervention module investigates short term effects of a computer based body exposure intervention and is described in detail in the following paragraphs. Ethical approval for the FRALANA study was granted by the local ethics committee of the Medical Faculty at the Friedrich-Alexander-University Erlangen-Nuremberg (ID: 257_20 B). The study is registered with the German Clinical Trials Register (Deutsches Register Klinischer Studien; DRKS), ID number DRKS00024675. The study is conducted in accordance with the Declaration of Helsinki. All adolescents and their parents, or young women, respectively, have to give informed consent before participating.

### Design

Within a randomized controlled trial (RCT) female adolescents and young women with AN are either receiving four sessions of a computer based body exposure intervention (AN-INT) or treatment as usual (AN-TAU). Additionally, a highly body dissatisfied group of clinical control participants (CG-INT) are undergoing the intervention to identify AN-specific processes of the intervention. The study design, including study groups, time points and methods of assessment, is shown in Figure 1. The study includes intraindividual (pre- vs. post-intervention; modifications throughout the four exposure sessions) and interindividual (AN-INT vs. AN-TAU; AN-INT vs. CG-INT) research. The TAU group only completes the pre- and post-intervention sessions with assessment of psychopathology and a recording of gaze patterns.

**Figure 1 F1:**
[figure not shown]
Study Design. The figure shows the sessions which the different groups complete (AN-INT, Anorexia Nervosa Group-Intervention; AN-TAU, Anorexia Nervosa Group-Treatment As Usual; CG-INT, Body Dissatisfied Control Group-Intervention) and how the groups will subsequently be compared. Within the RCT, adolescents with AN obtaining the intervention (AN-INT) vs. treatment as usual (AN-TAU) will be compared to each other. In a transdiagnostic approach, a body-dissatisfied group of clinical control participants (CG-INT) obtaining the intervention will be compared to AN-INT in order to identify AN-specific processes. Intraindividual processes will be analyzed for AN-INT and CG-INT.

### Target/Study Population

Participants must be between 10 and 21 years of age and of female gender. The following groups will be included in the study:

(1) AN patients (*AN*): Diagnosis of AN according to ICD-10 criteria (ICD-10: F50.0 or F50.1) diagnosed by an experienced (child) psychiatrist or psychologist using the “Kinder-DIPS” diagnostic interview (45, 46) in adolescents and the Structured Diagnostic Interview for Mental Disorders [DIPS; (47)] in adults;

(2) Body dissatisfied control group (*CG*): Patients with a high level of body dissatisfaction (according to the EDI-2 subscale “Body dissatisfaction“ [highest quartile = >75th percentile] and clinical judgment of an experienced (child) psychiatrist or psychologist).

At study inclusion, all children and adolescents are required to have a body weight > 10th BMI age percentile, or a BMI > 18.5 kg/m^2^ for young women, respectively, corresponding to a weight range above the classification of being underweight to avoid habituation at very low weight in AN participants. Participants will be recruited during inpatient, day clinic, or outpatient treatment at the Division of Child and Adolescent Mental Health and the Department of Psychosomatic Medicine and Psychotherapy. Antidepressant or antipsychotic medication is not an exclusion criterion; however, acute psychotic symptoms, use of illegal substances, medication with sedating effects, chronic somatic diseases, intellectual disability (IQ <85) and insufficient understanding of the German language are exclusion criteria.

Until now and to the best of our knowledge, no study using a comparable computer based body exposure intervention using photographs of the own body could be identified. Because of this, sample size calculation for the current pilot study was performed in accordance with former studies assessing effects of mirror (body) exposure in adolescents and adults with EDs (23, 42), as well as fear-stimulus exposure in phobic adolescents (48), reporting mostly medium effect sizes for body avoidance (body) anxiety and negative emotions. According to sample size calculations [G^*^Power; (49)] based on default values (alpha error =.05, power =.80) and the assumption that effect sizes for the RCT (AN-INT vs. AN-TAU) are expected to be larger than for the comparison of AN-INT vs. CG-INT, both taking part in the same intervention, at least 23 participants are required for the intervention groups (AN-INT, CG-INT) and at least 15 participants are required for AN-TAU. This is calculated based on a 2 × 2-mixed design (RCT; between-subject factor: AN-INT vs. AN-TAU; repeated measure within-subject factor: pre, post) and a 2 × 4-mixed design (AN-INT vs. CG-INT; repeated measure within-subject factor: 4 exposure sessions), respectively.

### Parameters

Psychopathology is assessed through the completion of multiple questionnaires: Eating disorder psychopathology and body dissatisfaction are assessed by administering the Eating Disorder Inventory-2 [EDI-2 (50), German version (51)], body image avoidance behavior via the Body Image Avoidance Questionnaire [BIAQ (52), German version (53)], and body checking behavior by the Body Checking Questionnaire [BCQ (54), German version (55)]. To assess relevant comorbid symptoms, we are also administering the Beck Depression Inventory-Revised [BDI-II (56), German version (57)] to test for depressive symptoms, and the Fear Survey Schedule for Children-Revised [FSSC-R (58), German version (59)] to test for symptoms of anxiety. Additionally, body parts are rated for self-perceived attractiveness on a seven point Likert-type scale (ranging from very negative to very positive) and participants are asked to list their three most disliked body parts. In order to control for a potential attention deficit we also administer an attention test [d2 test (60).

Attentional bias is assessed by recording gaze patterns during body exposure via the Eyegaze Analysis System^TM^ (Interactive Minds, Dresden, Germany), which is an infrared video-based binocular tracking system (17). In particular, the subsequent analysis is focused on assessing the fixation patterns (duration, frequency) on the previously three most negatively rated body parts, which are defined as regions of interest (ROI). A fixation is counted if the participant's gaze is focused on a specific area for 100 ms or more. Total fixation time for each ROI is calculated and corrected for its size relative to the picture size (17).

Stress levels and stress reactivity are assessed through multiple measures. Firstly, subjective emotion ratings (anxiety, anger, disgust, stress, and sadness) are obtained on a ten-point Likert scale before, during, directly after, and 30 min after each exposure session. Secondly, participants' cardiac activity is monitored during the exposure sessions using a Scosche^®^ Rhythm 24 Heart Rate monitor. Raw data is further processed using Python (https://www.python.org/). RR intervals (RRI) will be detected by a peak-detection algorithm and outliers will be removed using implemented python libraries (e.g., hrv-analysis 1.0.4 package). Instantaneous heart rate (IHR), as a measurement of heart rate variability (HRV), will be derived following IHR$=\frac{60000}{RRI}$, where RRI are measured in milliseconds (61). Changes in HR/IHR and RRI in relation to the number of exposure sessions, i.e., changes over the course of the four exposure sessions, will be analyzed. Thirdly, saliva samples are taken before, during (10 min into the exposure), directly after and 30 min after the body exposure using Salivettes^®^ (Sarstedt, Nümbrecht, Germany). Cortisol, as well as sAA, levels are subsequently analyzed in the laboratory. To do this, saliva samples are stored at −20°C until processing. When processing begins, the samples are thawed and centrifuged at 2,000 × g and 20°C for 10 min. To analyze salivary free cortisol, a commercial chemiluminescence immunoassay (CLIA; IBL Hamburg, Germany) is used, following the manufacturer's instructions. Similarly, to measure sAA, a quantitative enzyme kinetic method is employed, following a standardized protocol.

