## Introduction

Anorexia nervosa (AN) has a lifetime prevalence of between 0.5 and 2%, with a peak age of onset between 13 and 18 years (1). AN is characterized by abnormally low body weight, an intense fear of gaining weight, and a disturbed perception of the own body (2). AN is associated with poor outcomes: Mortality rates are high, and after treatment, less than one half of patients recover, whereas 20% remain chronically ill (3). Specifically, adolescent AN patients show high hospital readmission rates [45% after inpatient treatment (4)].

Body image (BI) is a multifaceted construct including perceptual, affective, cognitive, and behavioral components referring to the own and others' bodies (5). BI disturbances are diagnostic features and stabilizing factors in eating disorders (EDs): patients overestimate their shape and weight (6). Regarding behavioral aspects of BI disturbances, typical features in AN are body checking (repeated measuring and checking of shape and weight) and body avoidance [e.g., covering up the body shape by wearing baggy clothes or avoiding looking at oneself in the mirror (7)]. Despite much fewer studies on adolescents than on adults, a recent systematic review reported more BI disturbances in adolescents with AN and bulimia nervosa (BN) compared to healthy controls (8), similar to findings in adults. Alongside, Legenbauer, Thiemann (5) point out age-dependent differences between children, adolescents, and adults and the need for more studies for the still underresearched group of children and adolescents with eating disorders.

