## Objectives

Due to the high association of BI disturbances and the development and maintenance of EDs, including AN, psychotherapy with patients with AN in any setting should include modules treating body image disturbances explicitly (8). A need for new, emerging treatments with a focus on brain-based interventions as well as mechanism-based approaches, which are specifically addressing psychopathology and BI disturbances, have been proclaimed (43, 44). While there is data available on the efficacy of body exposure interventions for reducing BI disturbances in women with EDs and high body dissatisfaction (20, 25), there is a lack of available data regarding the efficacy of body exposures with children and adolescents. Furthermore, different EDs are frequently mixed up in the literature, making it difficult to investigate specific processes, which might differentiate between body dissatisfied individuals with EDs and body dissatisfied individuals without EDs. Also, underlying psychophysiological and neurobiological processes during body exposure are still poorly understood. Therefore, the aim of this study is to investigate the short-term efficacy of a computer-based body exposure intervention for adolescents with AN. This group is being compared to an AN-TAU group and a body dissatisfied clinical control group.

The primary research question is: Is body dissatisfaction in adolescents with AN reduced after completing a four-session computer based body exposure intervention, compared to TAU?

Secondary research questions include: (1) Body checking and avoidance: Can four sessions of a computer based body exposure intervention reduce body checking and body avoidance behavior, compared to TAU? (2) Viewing patterns / attentional bias (AB): Can the AB in terms of focusing more on negatively rated body parts, measured via eye tracking, be reduced by a four-session computer based intervention in adolescents with AN, compared to TAU? Are there AN-specific AB modifications in comparison to a body dissatisfied control group also obtaining the intervention? (3) Stress reactivity: Do four sessions of body exposure modify stress reactivity in terms of a physiological habituation, measured via salivary cortisol, sAA, HR and HRV? Are there AN-specific effects in physiological habituation in comparison to a body dissatisfied clinical control group?

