#### Body Exposure Sessions

The four computer based body exposure sessions are identical and involve a guided exposure to the previously taken photographs of the participant's own body on the computer screen. Standardized instructions are played to the participants via audio file and reactions and short descriptions of their body parts will be supervised by the study attendant who is present during the sessions. In the beginning and at the end of each session, there is a 30 s period of free viewing time for each the frontal and lateral photograph. During this time, participants are viewing the pictures without any instruction and eye movements are recorded in order to measure AB. The audio file guides participants in viewing their own bodies on the computer screen for an overall duration of about 30 min. The body exposure follows an adapted version of the manualized treatment program by Vocks and Legenbauer (62), in which participants are guided to look at 12 body parts following a fixed sequence. To assess stress reactivity, four saliva samples are taken before, during directly after and 30 min after the end of the body exposure with emotions being rated at the same times. Heart rate variability will be assessed continuously throughout each session via heart rate monitor. The standardized procedure of a body exposure session is shown in Figure 2.

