## Strengths and Expected Outcomes

The multi-level approach of this study allows for both an objective and a subjective evaluation of the short-term effects of the proposed computer based body exposure intervention. It will give new insights into the effects and underlying processes of the underresearched field of body exposure in adolescents with AN. The collected data will be assessing different aspects of body dissatisfaction and general psychopathology by employing questionnaires, measuring AB, utilizing emotion ratings, recording HR and HRV, as well as determining salivary cortisol and sAA levels, throughout the exposure sessions. Besides comparing the pre-post intervention effect with TAU within an RCT, this study will also investigate how the processes that underlie body exposure change throughout the intervention and if there are AN-specific modifications in comparison to adolescents with high body dissatisfaction (CG-INT). Corresponding with the current literature regarding body exposure interventions, especially for adolescents with AN, we expect psychopathology (body dissatisfaction, body image avoidance, body checking) to be reduced at the end of the intervention compared to the beginning of the intervention and with TAU and the AB to weaken (shown by spending less time looking at the negatively rated body parts). Furthermore, we expect a physiological habituation, both within and across sessions, with a decrease in emotion ratings, HR and neuroendocrine stress levels. To put it in a nutshell, results of this pilot study will give new insights into the effectiveness of and the processes underlying body exposure interventions in children, adolescents, and young women. Despite a relatively small sample size, a comprehensive in-depth analysis, implemented by multi-level assessment, will be carried out, thereby expanding the so far weak literature on mechanisms of BI disturbances and specific interventions for the abovementioned patient groups. The results of the current pilot study will be used for the design of a subsequent larger, multi-center intervention study with adolescents with AN, helping e.g., to identify modifiable BI and psychopathologic outcome measures, to select relevant and modifiable stress markers, and to provide orientation toward expectable effect sizes.

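### Attentional bias is scored from fixations on the three disliked body parts alone, so a change in overall viewing of the body is read as a change in bias

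*Protocol article*

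**What the plan says.** Under Parameters, the protocol article concentrates the gaze analysis on the duration and frequency of fixations "on the previously three most negatively rated body parts, which are defined as regions of interest (ROI"). The threshold is given: "A fixation is counted if the participant's gaze is focused on a specific area for 100 ms or more". The one adjustment described is for area: "Total fixation time for each ROI is calculated and corrected for its size relative to the picture size".

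Under Body Exposure Sessions, the recording takes place at the start and end of each session, where "there is a 30 s period of free viewing time for each the frontal and lateral photograph", with no instruction on where to look. AN-TAU has gaze recorded only in the pre- and post-intervention sessions.

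The construct is worded comparatively under Objectives: "Can the AB in terms of focusing more on negatively rated body parts, measured via eye tracking, be reduced". The Introduction gives the reference pattern in women without an eating disorder as attention balanced between body parts they rate positively and negatively. Strengths and Expected Outcomes gives the direction of benefit: it expects "the AB to weaken (shown by spending less time looking at the negatively rated body parts").

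Data Analysis puts AB into a 2 × 2 repeated-measures AN(C)OVA (AN-INT versus AN-TAU, pre and post) and a 2 × 4 one (AN-INT versus CG-INT, four sessions).

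**The concern.** A bias towards disliked parts means that they attract more attention than the rest of the body. The stated score holds only the first half of that comparison. No part of the article divides by total time on the body or contrasts the disliked parts with others. The score therefore mixes two quantities: how much the participant looks at her body, and how that looking is distributed.

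The first quantity is itself of clinical interest here. The Introduction lists body avoidance as typical of anorexia nervosa, including "avoiding looking at oneself in the mirror", and the Objectives ask whether the intervention reduces it. A treatment that changes overall viewing would move the AB score even if the distribution of gaze stayed the same. The article also says that this pilot will guide outcome selection and expected effect sizes for a larger multi-center study, so an AB effect that mixes the two would carry forward.

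**Working it through.** The article states no figure for this outcome, so there is none to reproduce. The check is how the score behaves.

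**Inputs from the article:** three ROIs; correction by ROI size relative to picture size; two photographs at 30 s each, so 2 × 30 = 60 s per assessment.

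**Assumed inputs:** on-body viewing times, shares of gaze and ROI areas. The documents give none. The article prints no equation for the size correction; I take it as division by relative area.

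**1. The score.** For ROI *k*, let T_k be fixation time and a_k its area as a proportion of the picture. Let B be total fixation time on the body and p_k = T_k / B. Then

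S = Σ T_k / a_k = B × Σ (p_k / a_k).

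**2. Change within a person.** With the same photographs and ROIs, each a_k is fixed. If the distribution of gaze over the body (the p_k) is unchanged, then

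S_after / S_before = B_after / B_before.

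The area correction cancels. For example, with a 30% share and on-body time falling from 25 to 20 s of one 30 s window, ROI time goes from 7.5 to 6.0 s. Dividing by an area of 5%, 10% or 15% gives 150 → 120, 75 → 60 or 50 → 40, which is −20% each time. If mean fixation length is constant, fixation frequency on the same ROIs changes in the same ratio.

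**3. Illustrations over the 60 s (assumed).**

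| On-body time, s | Share on disliked parts | ROI time, s | Change in score | Relative bias |
|---|---|---|---|---|
| 50 → 40 | 30% → 30% | 15 → 12 | −20% | unchanged |
| 50 → 30 | 30% → 30% | 15 → 9 | −40% | unchanged |
| 30 → 50 | 30% → 20% | 9 → 10 | +11% | weaker |

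The third row is the reverse error: avoidance falls, the bias weakens, and the score rises (10 / 9 = 1.11). In a single 30 s window, on-body time falling from 25 to 10 s while the share rises from 40% to 60% gives ROI time of 10 → 6 s. That is −40%, read as improvement, although the bias is stronger.

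**4. Where it enters the analyses.**

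- *AN-INT versus AN-TAU.* Only AN-INT views the photographs at length, about 30 minutes in each of four sessions. Any effect of this on overall viewing differs by arm and enters the group × time term. Randomisation still supports a fair comparison of ROI time; what it does not support is reading that comparison as a change in bias.
- *2 × 4 analysis.* AN-INT and CG-INT receive the same exposure. A change in on-body viewing common to both moves the session main effect. It reaches the group × session interaction only if the change differs by group (taking their initial shares as similar).

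**The case against.** The strongest reply is that this is a condensed article. Its wording states an emphasis rather than a full scoring algorithm, and the size correction rests on an earlier eye-tracking study that is not at hand. Gaze is recorded over the whole picture and all body parts are rated from very negative to very positive, so a relative index is not excluded. This has some force, and a fuller plan may contain one. But the article does state both the score and the direction read as benefit, and the two together do not match its own definition of the bias.

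The second reply is that avoidance is measured separately by the Body Image Avoidance Questionnaire and tested in the same 2 × 2 model. That is true, and worsening avoidance would not go wholly unexamined. The questionnaire does not measure gaze, however, and is not used to interpret the AB score.

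Three stronger readings are tempting and are not supported:

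- *Closed eyes and tracking loss count as improvement.* The article does not address invalid gaze data, and an article may leave that to a fuller document.
- *Disengagement over the sessions is likely, so the score favours the intervention.* Nothing in the article shows this. It expects avoidance to fall, which would push the score the other way.
- *Both comparisons are compromised throughout.* A change common to AN-INT and CG-INT leaves the AN-specific comparison largely alone, as shown in the working.

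**Conclusion.** The point holds for a secondary outcome. As described, the AB score cannot separate a change in relative bias from a change in overall viewing of the body, and the error can run in either direction. The proportional pass-through follows from the definition of the score, assuming fixed photographs and ROIs and a constant-factor size correction. The −20%, −40% and +11% figures are illustrations from assumed viewing times and shares. They show what is possible, not how likely or how large it will be in this trial. The primary comparison of body dissatisfaction does not use gaze data and is unaffected.

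**What to change.** Define the AB outcome, per assessment window, as the area-adjusted share of on-body fixation time on the three baseline-defined disliked parts:

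R = (Σ T_k / T_body) ÷ (Σ a_k / a_body),

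where T_body and a_body are summed over all body ROIs and R = 1 means attention in proportion to size. A contrast with the most positively rated parts is an acceptable alternative. Keep the planned ROI time and frequency as supporting measures, and report total on-body fixation time beside them so that a change in avoidance can be seen as such. Reword the expectation under Strengths and Expected Outcomes so that a lower share, not less time, shows a weaker bias. The article already largely implies ROIs fixed from the pre-intervention ratings, so nothing new is needed there.

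The cost is small: the gaze recordings and attractiveness ratings are already part of the procedure. ROIs for the remaining body parts must be drawn on each photograph. The share is also less stable when on-body time is short, which is a further reason to show on-body time alongside it.

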#### Pre-intervention Session

The pre-intervention session starts with the completion of the questionnaires, the attractiveness-ratings of the body parts and the attention test. Furthermore, some theoretical background regarding exposure therapy is explained (psychoeducation). Afterward, two photographs of the participant wearing standardized sportswear (black sports bra and tight shorts; one picture each in frontal and lateral view) will be taken. Lastly, the participant receives an introduction to the eye tracking methodology and the saliva collection technique. For the AN-TAU group, an assessment of AB is taken during this session.

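### Fixation time is corrected for region size relative to the picture rather than the body, so AN-INT versus CG-INT differences in gaze level can partly reflect on-screen body size

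*Protocol article*

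**What the plan says.** All references are to the protocol article.

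- **Score (Parameters).** The analysis concerns fixations on each participant's own "three most negatively rated body parts, which are defined as regions of interest (ROI"). The normalisation is fixed: "Total fixation time for each ROI is calculated and corrected for its size relative to the picture size".
- **Stimulus (Pre-intervention Session; Body Exposure Sessions).** The pictures are "two photographs of the participant wearing standardized sportswear", one frontal and one lateral. They are taken once, and the four identical sessions "involve a guided exposure to the previously taken photographs of the participant's own body on the computer screen".
- **Groups (Target/Study Population).** Participants are "required to have a body weight > 10th BMI age percentile, or a BMI > 18.5 kg/m^2^ for young women". The limit applies to everyone, and no upper limit is given. CG-INT is recruited as "Patients with a high level of body dissatisfaction", with no matching on body size mentioned.
- **Question (Objectives).** For gaze, the comparison with CG-INT asks: "Are there AN-specific AB modifications in comparison to a body dissatisfied control group also obtaining the intervention"?
- **Model (Data Analysis).** A 2 × 4 repeated-measures AN(C)OVA, group by session, in which main effects, interactions or both may be interpreted depending on the hypothesis. Age and depression are named as examples of covariates. Outcomes are log-transformed only if test requirements fail.

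**The concern.** Correcting for region size is meant to stop a large body part from collecting more gaze merely because it is large. When every participant views the same pictures, dividing by the region's share of the picture achieves this, and any remaining factor is common to all. The Introduction describes the earlier eye-tracking study cited for the correction as using pictures of female bodies. If those pictures were common to all participants, the issue could not arise there.

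Here the picture is of the participant herself. A body that fills less of the frame has smaller regions, so the same seconds of fixation are divided by a smaller number and the score rises. If AN-INT and CG-INT differ in on-screen body size, a difference in their gaze levels can appear with no difference in attention. That matters for a pilot meant to guide the choice of outcome measures and the expected effect sizes of a larger trial.

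**Working it through.** **What can be reproduced.** The plan gives no number for the gaze score. Its only figure for this comparison is 23 participants per intervention group. That figure cannot be recomputed, because neither the effect size nor the correlation between sessions is given, and it is not disputed here.

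**Step 1: the score under on-body gaze.** Let T be viewing time and A_roi, A_body and A_pic the areas of the region, body and picture. If all gaze falls on the body in proportion to area, region time is T × A_roi/A_body. Dividing by A_roi/A_pic gives

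score = T × A_pic/A_body.

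The region cancels and body size remains. With the documented T = 30 s per view and an assumed region of 15% of the body, region time is 4.5 s:

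| Body share of picture (assumed) | Region share of picture | Score, picture denominator | Score, body denominator |
|---|---|---|---|
| 15% | 0.0225 | 200 | 30 |
| 20% | 0.0300 | 150 | 30 |
| 25% | 0.0375 | 120 | 30 |
| 30% | 0.0450 | 100 | 30 |

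**Step 2: from BMI to score.** Assume equal height, equal framing and silhouette width proportional to √BMI. The score ratio, thinner to heavier, is √(BMI₂/BMI₁):

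- 19 vs 22: √1.158 = 1.076
- 19 vs 25: √1.316 = 1.147
- 19 vs 30: √1.579 = 1.257

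If 20% of gaze is instead spread over the whole picture, the score is T × (0.8 × A_pic/A_body + 0.2). Taking a 20% body share for the thinner person, the ratios become 1.07, 1.14 and 1.24. For the last: (0.8/0.20 + 0.2)/(0.8/0.2514 + 0.2) = 4.20/3.38.

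**Step 3: effect on the tests.** Simulation with 23 vs 23, four sessions, lognormal scores, session correlation 0.5 and 10,000 runs per setting. Gaze behaviour is identical and only the ratio from Step 2 differs. The interaction is tested as a linear trend over sessions. Ranges run from between-person CV 0.5 to 0.3; nominal level 5%.

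| Ratio | Group main effect | Group × session, no change in gaze | Group × session, both fall 30%, raw scale | Same, log scale |
|---|---|---|---|---|
| 1.076 | 10–18% | about 5% | 5.5–5.9% | about 5% |
| 1.147 | 21–49% | about 5% | 6.4–8.3% | about 5% |
| 1.257 | 49–89% | about 5% | 7.7–13.5% | about 5% |

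The pattern follows from the photographs being fixed: each participant's factor is constant over sessions. It shifts her level but creates no trend. It only rescales a trend that is there. At ratio 1.147 a 30% fall is 0.30 × 1.147 = 0.344 units against 0.300, whereas on the log scale both groups fall by the same ln 0.7.

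**The case against.** **The gaze question is about change, not level.** This stands. The Objectives ask about modification, which points to the group-by-session term, so the large main-effect error rates are not error rates for the stated question. The main effect stays relevant only because Data Analysis allows main effects to be interpreted.

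**A body-size difference between the groups is not shown.** This also stands. Both groups share the lower weight limit and no group BMI is given. A reader might infer that AN-INT versus CG-INT gaze differences do measure body size. The document supports only that they can.

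**Framing is not described.** An article may leave this to the full protocol, so the silence is not a fault, but the result depends on it. A reader might infer a large height artefact from the 10-to-21 age range. At a fixed camera distance, 1.50 m versus 1.70 m would give (1.70/1.50)^1.5 to (1.70/1.50)² = 1.21 to 1.28. If photographs are scaled to a common height, body share varies with √(BMI/height) and the shorter participant scores √(1.50/1.70) = 0.94 times as much. The direction reverses, so no height claim is made. The BMI effect remains under either framing.

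**The neutral denominator depends on how gaze behaves.** If gaze were spread evenly over the whole picture, the picture denominator would be neutral (30 at every body size) and the body denominator would not be. For viewing a photograph of one's own body, gaze mainly on the body is the more likely case, but it is an assumption.

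**The covariate list is open.** BMI is not excluded, so its absence from the examples is no finding.

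**Conclusion.** The point holds in conditional form and is a cheap improvement, not a serious flaw. The stated correction leaves on-screen body size as an uncontrolled factor in between-group gaze levels. If AN-INT and CG-INT differ in that respect, the thinner group scores about 8% to 26% higher for the same on-body gaze, given assumed BMIs of 19 versus 22 to 30, equal framing and square-root scaling. The CVs and session correlation behind the error rates are also assumptions.

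A reader might go further and conclude that the AN-specific gaze question is invalidated or that the RCT gaze result is biased. The document supports neither. The interaction keeps about its nominal level if gaze does not change, is inflated moderately on the raw scale if both groups improve, and is unaffected on the log scale. In AN-INT versus AN-TAU, randomisation leaves no systematic difference in body size.

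**What to change.** In Parameters, express region size relative to the area of the participant's body in the photograph, using one silhouette outline per photograph. In Data Analysis, state that AN-INT versus CG-INT change in attentional bias is analysed on a log or percent-of-baseline scale from the outset, not only when test requirements fail. A participant's constant factor then drops out of the interaction whichever denominator is used. The picture-based score can be kept as a secondary version for comparability with the earlier eye-tracking study.

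The cost is two outlines per participant, on photographs the study takes anyway, with no new data collection. The log scale needs a rule for regions with no fixation. Some dependence remains if gaze leaves the body, but it is small: with 20% of gaze spread over the picture and body shares of 20% and 25.14%, the body-based scores are in the ratio (0.8 + 0.2 × 0.20)/(0.8 + 0.2 × 0.2514) = 0.840/0.850, about 1% apart instead of 24%.

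A BMI covariate or an analysis restricted to overlapping BMI is at most an optional sensitivity check. BMI is tied to diagnosis, so adjusting for it may remove part of the group difference of interest, and an overlap subset of 23 versus 23 would be small. No change to the weight criterion is implied.
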